**Fig. 2 Fig2:**
[figure not shown]
Screenshots of electronic medical record tools for atrial fibrillation. **a** Atrial fibrillation toolbar. **b** Structured template for atrial fibrillation initial assessment. **c** Structured template for atrial fibrillation follow-up visit. **d** Chart-based clinical decision aid for calculating stroke and bleeding risk. **e** Physician reminders for INR tracking and overdue renal function testsTemplates for initial assessment or routine follow-up of patients with AF (Fig. 2b, c): Our pilot project provided strong impetus for the development of guided clinical encounter forms. Clinicians desired prompts regarding the essential items to cover when seeing a patient with AF and wanted to retain flexibility to respond to such prompts according to the competing priorities of a given encounter. With these principles in mind, we included in the toolkit EMR-based “custom forms” (i.e., templates) that can be inserted within the progress note. These follow a typical SOAP note format (i.e., subjective, objective, assessment, plan) familiar to family physicians and facilitate a brief assessment of both quality of life and adherence to stroke prevention treatment.AF-related stroke and bleeding risk calculator (Fig. 2d): Counseling regarding risks and benefits is challenging, even for patient/provider dyads with high numeracy. Primary care physicians often experience discordance when attempting to both integrate shared decision-making ideals and meet guideline recommendations [69]. This tool aids the provider to quickly calculate both risk of stroke with and without treatment and the risk of bleeding. The output will remind patients and providers that risk of stroke and risk of bleeding should not be weighed evenly, given that impact on quality-adjusted life-years (QALY) for bleeding is much smaller than for stroke.Reminders for INR tracking or overdue for renal function (Fig. 2e): Even if prescribed with warfarin, evidence suggests that patients may be in therapeutic range only about half the time [70]. Patients attending anticoagulation clinics with systematic, protocol-driven approaches to warfarin dosing spend more time in therapeutic range, while other physicians may have a tendency to underdose rather than overdose warfarin [71]. The goal of this tool is to provide physicians (or pharmacists associated with intervention clinics) with a system for tracking patients taking warfarin and assist providers in adjusting warfarin dose according to the INR result.

### Implementation support

A previous study examining a quality improvement intervention in Ontario found that even multidisciplinary primary care teams failed to take action upon receiving feedback reports indicating substandard performance on chronic disease management due to a lack of “performance management skill development” [72]. At the same time, high-cost interventions are unlikely to be scalable or replicated. Therefore, we aim to offer implementation support in a manner that could be sustainable, as described below.

With notification that the SAFIRE feedback is available, intervention clinics will be offered a virtual group presentation (i.e., a webinar) by research team members familiar with both the toolkit and the clinical aspects of AF. In advance of this meeting, we will attempt to identify local physician champions and key non-physician participants (i.e., data retrieval delegates) at each intervention clinic. The educational aspect of the presentation will review the guideline summary including approaches for risk assessment and information about NOACs and then introduce the functionality of the online feedback platform. Although the feedback is confidential for each physician, participants will be encouraged to discuss the results among their teams, providing an opportunity to problem solve and share best practices. The group presentation will also be used to introduce the EMR-based features of the toolkit. Research staff will then provide support to clinic administrators to install and activate the EMR-based tools. (The EMR-based reminders or tools can be “turned off” by the providers at any time.) Any participants not able to attend the group meeting will be provided with a video recording of the webinar and offered a personal phone meeting with similar objectives. One month after the initial presentation, each clinic will receive invitations for one-to-one assistance to troubleshoot any problems arising with the intervention components and to offer again help implementing the toolkit. With new feedback approximately 6 months later, research staff will contact the physicians via email to prompt them to review updated feedback reports, an infographic designed to encourage interest in improving the management of AF [Additional file 2], as well as to offer support for implementing or using the toolkit.

### Outcomes

The primary outcome is the proportion of patients with AF and an estimated yearly risk of stroke greater than 2% who are receiving stroke prevention therapy after one year. Specifically, the denominator will be patients aged ≥ 65 or who have a CHADS2 score ≥ 1. Offering such patients anticoagulation would be concordant with the 2014 CCS Guidelines [13]. Although the guidelines indicate that NOACs may be preferable over warfarin, we will group all anticoagulants together for the primary outcome because warfarin remains a suitable option for many patients. We acknowledge that anticoagulation may not be advisable in all these patients (e.g., high risk of bleeding, severe cognitive dysfunction making compliance unreliable, patient preference, etc.). However, it is impractical to accurately adjudicate appropriateness of withholding the anticoagulant using chart reviews alone given variability in charting practices and it is expected that the trial design will balance such patients across the study arms.

Secondary outcomes include the proportion of patients with the following characteristics: no CHADS2 risk factors and age <65 receiving anticoagulation; taking warfarin with at least six INRs measured per year; taking warfarin and time within a therapeutic range >60% using the Rosendaal method [73]; taking a NOAC with appropriate dosing (based on age and/or renal function); taking a NOAC but without renal function measured in 6 or 12 months; receiving other antiplatelets (e.g., aspirin alone, clopidogrel alone, aspirin plus dipyridamole, aspirin plus clopidogrel); taking an oral anticoagulant in combination with single or dual antiplatelet therapy; blood pressure (BP) and low-density lipoprotein (LDL) at target (to assess control of other stroke risk factors).

Process outcomes include the proportion of patients with AF in the cumulative patient profile, the proportion of patients with a formal stroke risk assessment completed, the proportion of patient charts with EMR-based tools used, and the proportion of providers who accessed the SAFIRE website to review their quality of care metrics.

### Measurement

EMR-based treatment data will be used to identify stroke prevention therapy. Previous work with EMRALD has shown that EMR data regarding active treatments (e.g., warfarin) is comparable to administrative data in terms of drug-capture for patients over age 65 (and far superior for patients under age 65 as drug administrative data in Ontario is limited in patients under 65) [16, 53]. To determine whether the stroke prevention therapy is concordant with guideline recommendations, the EMR data will be used to identify whether patients have relevant comorbidities (i.e., CHADS2 risk factors). The EMRALD team has validated, automated methods for identifying patients with diabetes [55, 74], ischemic heart disease [75], and hypertension [76] using data from both structured fields and free text. Patients identified with these conditions and relevant quality indicators are already included in the online feedback platform.

We developed a strategy for centralized identification of patients with AF in EMR data by performing a sensitive search for patients with a possible diagnosis of AF in the patient profile or with relevant treatments and/or results of cardiology tests that implicate a diagnosis of AF. An EMRALD team physician verified the charts to remove false positives from the study cohort, such as those with only brief runs of AF or those with only transient AF following surgery and follow-up testing that was normal. The methods for developing the search are similar to those used in previous studies [77] and based on previously described patient populations [16]. This search algorithm identified AF patients with one or more of the following components: (1) Recording of AF, including paroxysmal AF, “fibrillation”, and “flutter” in the problem list or history of past health fields of the EMR record [Additional file 3]; (2) electrocardiogram (ECG) and Holter monitor reporting AF; or (3) OAC prescription without clot, thrombosis, embolism, DVT, PE, valve replacement in the problem list, or history of past health fields, in combination with calcium channel blockers (CCB), ß-blockers, or digoxin prescription. The algorithm was able to accurately identify AF patients with a sensitivity of 78.6% (95% CI, 72.6–83.9%), a specificity of 99.9% (95% CI, 99.8–99.9%), positive predictive value of 95.1% (95% CI, 90.8–97.7%), and negative predictive value of 99.4% (95% CI, 99.1–99.5%). In addition, we developed and validated automated algorithms for identification of stroke and congestive heart failure to enable estimation of CHADS2 risk factors [78].

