### Participants

Participants will be drawn from the primary care practices associated with the Electronic Medical Record Administrative data Linked Database (EMRALD) in Ontario, Canada. EMRALD is a unique data source that captures complete clinical patient charts already being used by family physicians (thereby avoiding the need for case report forms) [53, 54]. The electronic medical record (EMR) data are extracted and securely stored at the Institute for Clinical Evaluative Sciences (ICES), where it can be linked to population-level administrative health databases. EMRALD provides an opportunity for large-scale initiatives by facilitating centralized, automated chart abstraction, and data analysis using validated database algorithms to assess and provide feedback regarding quality of care. The platform has been used before to facilitate a quality improvement trial [55].

Eligible physicians are those participating in EMRALD, using PS Suite® EMR for at least 2 years, and have 100 or more rostered patients. These eligibility criteria are to ensure that physicians have had sufficient experience with their EMR and have adequate patient data to assess baseline and outcome measures. Eligible patients within EMRALD will have a physician diagnosis of AF recorded in their chart and >18 years of age. No distinction will be made between paroxysmal, persistent, and permanent AF. Analysis will be restricted to adult patients rostered to participating physicians since physicians may not start long-term medications for patients who are not regularly seen at their practice (thus excluding encounters such as “walk-in” patient visits).

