### Analysis

Outcomes will be compared at study completion at the patient, provider, and clinic levels. The analysis will be carried out on patient level variables using the generalized estimating equation approach to control for the effects of clustering. We will also adjust for the proportion of patients with guideline-concordant stroke prevention therapy at baseline and the other variables used in the minimization, as recommended by Taves [60]. Analysis will be performed on an intention-to-treat basis, and patient identifiers will be removed before transferring the data securely to analysts so that they will be blind to allocation. We will conduct the analysis as a longitudinal cohort design to permit exploration of patients whose treatments changed over time. As a sensitivity analysis, we will also conduct a repeated cross-sectional analysis to capture patients with newly developed AF during the intervention.

In keeping with similar trials in this literature, we considered a 10% difference in the primary outcome to be clinically important [48]. We assumed that 50% of patients with atrial fibrillation assigned to the usual care arm receive the primary outcome—using a control arm proportion of 50% is a conservative approach as it provides the largest sample size estimation. An EMRALD manual chart review of 7500 randomly selected adult patient charts discovered 192 patients with AF [16]; this 2.6% prevalence is similar to what has been reported in other primary care studies [79]. Based on that pilot data, we estimated that at least 100 patients would be available in each clinic (cluster). Therefore, using a reported intra-cluster correlation = 0.029 for warfarin uptake in patients with AF in primary care clinics [46], setting alpha = 0.05, and after adding 10% inflation for patient loss to follow up, 3276 patients (33 clinics) would be required to have 80% power [80].

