We acknowledge several potential limitations. First, the approach to delivering the interventions as a toolkit will make it difficult to determine which particular tools are most effective. While this approach will lead to variation in intervention uptake, it improves external validity, mimicking the real-world setting where providers will only adopt strategies perceived as useful in their context and for their patients. Second, although we have carefully developed tools to address known barriers, it is possible that other interventions may be valuable additions to the current approach or that the tools used will not be optimally tailored for the context. We have attempted to partially address this through a pre-trial phase including a mixed-methods pilot test in which the entire toolkit was tested in a primary care clinic, in keeping with the existing guidance for the development of complex interventions [82]. Third, our primary outcome is a process measure (i.e., appropriate prescribing) rather than a patient-oriented measure (e.g., stroke). We believe this is reasonable given the well-established effectiveness of stroke prevention therapy and believe this compromise is necessary given our desire to complete the analysis in a reasonable time frame. Fourth, our automated assessment of risk factors will be limited to data available in the EMR, and there is variation in the charting habits of family physicians. This may result in challenges for identification of patients with AF; patients with AF that cannot be readily identified will not be included in feedback reports and will not have the AF toolbar activated in their EMR chart. However, variation in charting is expected to be independent of randomization thus limiting risk of misclassification bias. Medications are entered as a structured variable in the chart and should not be affected by idiosyncratic data-entry. We recognize that some primary care clinics may be more likely to refer management of AF to consultants, but again expect that such characteristics would be independent of randomization. Further, if the rate of anticoagulation is far higher than expected, as seen in some studies [17], then we may encounter a ceiling effect. It is also possible that a ceiling effect may be reached due to external factors, such as attention given to this area by pharmaceutical companies. However, we may still find other results of interest in our analysis, including measures related to safety (i.e., appropriately frequent blood work). Finally, it is important to note that participants in EMRALD are a convenience sample of Ontario family physicians using PS Suite® EMR. This may make it difficult to generalize to other providers who use different EMR systems, or to those not using EMR at all. Nevertheless, most of the EMR strategies in the toolkit could be easily adapted to other systems.

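### The AF search partly selects on the primary outcome: this may dilute the cohort analysis, and it can make the denominator of the repeated cross-sectional analysis depend on arm

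*Protocol article*

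**What the plan says.** The Measurement section describes a three-part search: "This search algorithm identified AF patients with one or more of the following components". Component 1 is an AF entry in the problem list or past-history fields, and component 2 is an ECG or Holter report of AF. Component 3 is based on treatment: "OAC prescription without clot, thrombosis, embolism, DVT, PE, valve replacement in the problem list" or the past-history fields, plus a calcium channel blocker, beta-blocker or digoxin. Chart review follows, with one stated purpose: "An EMRALD team physician verified the charts to remove false positives from the study cohort". Sensitivity of the algorithm is 78.6%, given overall and not by treatment status or component.

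The Participants section words eligibility differently: "Eligible patients within EMRALD will have a physician diagnosis of AF recorded in their chart".

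Under Outcomes, all anticoagulants are grouped as success for the primary outcome, and AF charting is itself measured: "Process outcomes include the proportion of patients with AF in the cumulative patient profile". The section on EMR-based decision support says the AF toolbar appears only for patients with AF in that profile.

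The Analysis section makes a longitudinal cohort the main analysis and adds a sensitivity analysis: "we will also conduct a repeated cross-sectional analysis to capture patients with newly developed AF during the intervention". Under Strengths and limitations the authors expect that "variation in charting is expected to be independent of randomization thus limiting risk of misclassification bias".

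**The concern.** Take two patients with AF who are missed by components 1 and 2, one on an anticoagulant plus a rate-control drug and the other untreated. The search can find the first and not the second. Entry to the denominator therefore depends on the numerator. Removing false positives does nothing about this, because the problem lies in the false negatives.

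The two analyses are affected differently. A cohort identified before allocation carries the same enrichment in both arms. The cost is a smaller observable effect, since fewer patients are available to start treatment. In the repeated cross-section, patients also enter after randomization. One may enter because an anticoagulant was started, which is what the toolkit aims at. Another may enter because AF was newly charted, which the trial counts as a process outcome. Both may differ by arm, so the denominator can depend on arm and on treatment. Balance at baseline does not protect against that.

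**Working it through.** **Step 1. The plan's own figure.** Inputs from the Analysis section: 50% in usual care, a 10-point difference, alpha 0.05 (two-sided assumed), 80% power, intra-cluster correlation 0.029, 100 patients per clinic, 10% inflation.

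- Per arm, unclustered: (1.960 + 0.842)² × (0.5×0.5 + 0.6×0.4) / 0.10² = 384.6.
- Design effect: 1 + 99 × 0.029 = 3.871.
- Total: 2 × 384.6 × 3.871 = 2977.5; × 1.10 = 3275.3, against 3276 stated. It reproduces.
- Effective patients per arm: 3276 / 1.10 / 3.871 / 2 = 384.7.

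**Step 2. Enrichment of a fixed cohort.** The component-3-only share is not in the document, so this is an illustration over a range. Assumptions:

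- True anticoagulation is π = 0.50. This applies the plan's figure to all AF patients and ignores the age/CHADS2 restriction.
- Overall sensitivity is S = 0.786.
- Components 1-2 find treated and untreated patients equally often (s0).
- Component 3 catches a fraction q of the treated patients whom components 1-2 miss.

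Then S = s0 + πq(1 − s0), which gives:

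- s0 = (S − πq)/(1 − πq)
- sensitivity in treated patients: st = s0 + (1 − s0)q
- treated proportion in the cohort: c = π·st/S
- component-3-only share: πq(1 − s0)/S

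A toolkit that starts 20% of untreated patients (10 points over all AF) moves the cohort by 0.20(1 − c). Power is Φ(d/√{[a(1−a)+b(1−b)]/384.7} − 1.96), with a = c, b = c + d and d that difference.

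Worked case, q = 0.50: s0 = (0.786 − 0.25)/0.75 = 0.715; st = 0.715 + 0.285×0.5 = 0.857; c = 0.5×0.857/0.786 = 54.5%; effect 0.20×0.455 = 9.1 points.

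| q | Component-3-only share | Treated at baseline | Cohort effect (points) | Power |
|---|---|---|---|---|
| 0.10 | 1.4% | 50.7% | 9.9 | 79% |
| 0.25 | 3.9% | 51.9% | 9.6 | 77% |
| 0.50 | 9.1% | 54.5% | 9.1 | 73% |
| 0.75 | 16.3% | 58.2% | 8.4 | 67% |
| 1.00 | 27.2% | 63.6% | 7.3 | 58% |

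The last row is the limit: with every treated patient found, c = 0.50/0.786 = 63.6%, so enrichment lies between 0 and 13.6 points.

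**Step 3. The repeated cross-section.** Suppose the toolkit raises detection by components 1-2 by 10 points in its arm (assumption): s1 = s0 + 0.10 and st1 = s1 + (1 − s1)q. The observed proportion there is p·st1/[p·st1 + (1 − p)s1], with p = 0.50 for no prescribing effect and p = 0.60 for a true 10-point effect. The control arm stays at c.

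Worked case, q = 0.50 and no prescribing effect: 0.907/(0.907 + 0.815) = 52.7%, against 54.5%, a difference of -1.8 points.

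| q | No effect, charting +10 | True 10, charting unchanged | True 10, charting +10 |
|---|---|---|---|
| 0.10 | -0.4 | 10.0 | 9.6 |
| 0.25 | -0.9 | 9.9 | 9.0 |
| 0.50 | -1.8 | 9.7 | 8.0 |
| 0.75 | -2.8 | 9.4 | 6.9 |
| 1.00 | -3.8 | 8.8 | 5.4 |

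At q = 0.50 the same toolkit effect reads 9.1 points in the fixed cohort, 9.7 in the cross-section without a charting change and 8.0 with one. Agreement or disagreement between the two analyses would then partly reflect case-finding.

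**The case against.** Several objections have force, and each limits the point.

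- **Share unknown.** Component 3 also needs a second drug class and no listed alternative indication, and many such patients will qualify by component 1 or 2 as well. The share may be negligible. A reader might infer that the cohort is loaded with patients at ceiling; the document does not show that.
- **Treated patients are not fixed at success.** The outcome is measured after a year, the background notes that persistence declines, and Table 1 lists non-adherence as a target. The losses in Step 2 hold these patients at 100% in both arms, so they are upper bounds for each assumed share.
- **The 50% and 10 points may already describe the identified cohort.** If so, the planned power is not eroded. Step 2 also ignores the planned adjustment for baseline therapy.
- **The main comparison is protected.** The minimization covariates include clinic counts of AF patients and of anticoagulated at-risk patients, and the analysis adjusts for baseline therapy. A reader might infer that the primary contrast is biased; for a cohort identified before allocation, it is not.
- **Eligibility wording.** A patient found by component 3 may have AF recorded elsewhere in the verified chart. The two sections need aligning, but a flat contradiction is not established.
- **Effect on charting is an inference.** It rests on the process outcome and the toolbar trigger; no listed tool is described as prompting an AF entry. Patients not identified also get no feedback entry or toolbar, which limits how far the toolkit reaches them.

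None of this answers the cross-sectional problem. Its purpose is to add patients identified after randomization, and one entry route is the outcome itself.

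**Conclusion.** The point holds as a defect of ascertainment, mainly in the sensitivity analysis. Component 3 selects on the primary outcome, and verification does not correct this. In a cohort identified from pre-allocation data the consequence is a possible dilution common to both arms. Its size is unknown: under the stated model it runs from 0.1 point (1.4% share) to 2.7 points (27.2% share, the limit). The document implies such a cohort but gives no identification date.

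In the repeated cross-section the denominator can depend on arm and treatment. The expectation that charting is independent of randomization is reasonable for baseline ascertainment but does not cover this analysis. Under the assumed 10-point charting gain the spurious difference is -0.4 to -3.8 points. A reader might infer that the bias could equally favour the toolkit, or that the cross-section is worthless as a check. Neither is shown: every modelled reading is at or below the true effect, and at small q the distortion is slight.

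**What to change.** 1. Keep the primary cohort as the three-component search defines it, and state that it is fixed on data dated before allocation.
2. Report the component-3-only share by arm, and repeat the primary analysis with components 1-2 only as a sensitivity analysis.
3. In the repeated cross-section, do not admit new AF patients by component 3. Add a version that defines new AF by ECG or Holter reports only, applied identically in both arms, because component 1 remains open to differential charting.
4. Limit the independence statement under Strengths and limitations to baseline ascertainment, and align the eligibility wording under Participants with the search.

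The cost is a filter on an existing search plus wording. The secondary runs will have somewhat lower sensitivity and fewer patients, and the published validation figures apply only to the three-component algorithm. That is the reason to leave the primary cohort definition unchanged.
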